**Fig. 2 Fig2:**
[figure not shown]
*eMindYourHeart* intervention and timeline

## Randomisation, blinding and treatment allocation

Patients will be randomised 1:1 to **(i)** TAU + *eMindYourHeart* intervention to treat psychological comorbidity versus **(ii)** TAU alone. The randomisation will be stratified by site and stable versus unstable IHD. Randomisation will be performed in the internationally recognised data capture platform – Research Electronic Data Capture (RedCap) – by an independent researcher who will be blinded to the allocation list. Patients and therapists will be informed of treatment allocation after randomisation is final. A merged blocks permutation stratified by inclusion centre will be used. This adaptation of a stratified block randomisation is better suited to small clinical trials where regular block randomisation would compromise predictability [39]. The randomisation list will be created using the mergedblocksmulti function of the mergedblocks package in R3.6.0 for Windows [40] and will only be accessible to the researcher who created the list (RK). Apart from the psychologists delivering the therapy, the research team will be blinded to treatment allocation. Due to the nature of the intervention, it is not possible to blind patients to their trial condition.

## Intervention

### Development

We developed the *eMindYourHeart* intervention specifically for and with involvement of the target group (patients with IHD and comorbid depression, anxiety or both), using a user-centred design.

### Contents

The *eMindYourHeart* intervention is based on the principles of Cognitive Behavioural Therapy and include aspects from Acceptance and Commitment Therapy and Compassion Focused Therapy [41]. The intervention consists of an introductory module, 9 core treatment modules and 2 optional modules (related to sleep and lifestyle changes, respectively) (Table 2). As part of the intervention, patients will be asked to complete the CORE-10 in weeks 1, 2, 3, 5 and 7 and in additional weeks if the psychologist considers it necessary. The CORE-10 is used as an evaluation tool in therapy to evaluate the patient’s progress (http://www.coreims.co.uk/About_Measurement_CORE_Tools.html). See Fig. 2 for the *eMindYourHeart* intervention and timeline. Patients will also receive 4 phone calls as part of the intervention in weeks 1, 3, 6, and 9 (Fig. 2**)** and on a need to basis, as determined by the psychologist.

**Table 2 Tab2:**
[figure not shown]
Overview of the modules of the *eMindYourHeart* intervention

Psychologists will interview patients randomised to the intervention arm over the phone, using motivational interviewing and a brief purpose-designed interview protocol that includes elements from the Schedules for Clinical Assessment in Neuropsychiatry (SCAN) interview. The purpose of the interview is to gain information about the patient and the patient’s situation, equivalent to a standard anamnestic assessment.

Patients are expected to complete the intervention within a 12-week period. All patients will have access to the intervention up to 6 months post intervention, enabling patients to revisit the material and reuse it ad libitum. The intervention is protocolised by means of a treatment manual to ensure fidelity and is somewhat flexibly targetable to the individual patient’s needs and preferences. These include adding additional time to the treatment from the standard 9 weeks all the way to 12 weeks, helping patients with sleep and lifestyle changes through the extra (optional) modules, giving specific psychological tools based on CBT to patients with needs not addressed in the standard treatment [e.g. stress management tools], and the possibility of extra phone calls.

Patients will gradually work through the modules and communicate with the psychologists via a secure online platform through asynchronous text messages. The therapist receives messages from the patient and notifications about the patient’s treatment course. Psychologists and master’s students in psychology from the University of Southern Denmark will provide the intervention. They are supervised by licensed psychologists, who are part of the project team. Internet-delivered treatment targets the same core treatment processes as in face-to-face treatment – only the mode of delivery is different [23].

### Delivery

Patients in the intervention group will receive access to a General Data Protection Regulation (GDPR) Directive compliant platform. Users login with their personal digital signature from the public Danish authorities (NemID). The eHealth platform/app is built around the core of the Drupal Content Management System and written in the programming language PHP. The Drupal platform is designed and maintained by a global community of thousands of programmers. Drupal is available under the GNU General Public License v2, which allows for free use, modification and distribution.

## Treatment as usual

All patients, irrespective of treatment condition that they are assigned to, will receive TAU. In Denmark, patients with IHD are referred to CR 1–2 weeks after discharge from the hospital, with CR focusing on physical training, risk factor control and clinical follow-up and maintenance of the patients’ targets, patient education (e.g. nutrition, smoking etc.), screening for depression and anxiety, and addressing psychosocial issues [14, 15].

## Trial outcomes

Primary: Symptoms of depression, measured with HADS at the end of the intervention (i.e., 3 months).

Secondary: Symptoms of anxiety measured with HADS at 3 months; symptoms of depression and anxiety at 6- and 12 months’ follow-up; QoL (HeartQoL) at 3, 6, and 12 months follow-up; trial dropout (number of patients dropped out in either arms at 3 months) and cost-effectiveness/cost-utility.

## Patient-reported measures

Table 3 provides an overview of the patient-reported and related measures and their time of assessment used in *eMindYourHeart.* Standardised and validated questionnaires are supplemented with purpose-designed questions (e.g. to tap into patient satisfaction with CR).

**Table 3 Tab3:** Patient-reported outcome measures used and times of assessment

Construct assessed	Measure	Items	***Baseline***	***End of treatment***	***FU*** ***6 months***	***FU*** ***12 months***
Anxiety	Hospital Anxiety and Depression Scale (HADS-A)	7	X	X	X	X
Depressive symptoms	Hospital Anxiety and Depression Scale (HADS-D)	7	X	X	X	X
Anxiety symptoms	Cardiac Anxiety Questionnaire (CAQ-18)^1^	18	X	X	X	X
Depressive symptoms	Patient Health Questionnaire (PHQ-9)^1^	1	X	X	X	X
Loneliness	UCLA Loneliness Scale	3	X	X		
Social support	Multidimensional Scale of Perceived Social Support (MSPSS)	12	X			
Illness perceptions	Brief Illness Perceptions Questionnaire (B-IPQ)	9	X			
Quality of Life	HeartQoL	14	X	X	X	X
Perceived stress	Perceived Stress Scale	10	X	X	X	X
Health Anxiety and Somatic Complaints	Health Complaints Scale	24	X	X	X	X
Physical activity	Purpose-designed	2	X	X	X	X
Patient’s engagement in general CR	Purpose-designed	4		X		
Potentially negative effects of treatment	The Negative Effects Questionnaire (NEQ)^a^	20		X		
Cost-effectiveness/cost-utility^2^	EQ-5D-5L	6	X	X	X	X
Patient expectations to CR	The credibility/ expectancy questionnaire (CET)^a^	4	X			
Patient satisfaction with / evaluation of eHealth intervention	Internet evaluation and usability questionnaire^a^	6		X		
Patient satisfaction with CR	Purpose-designed measure	1		X		

*FU* Follow-up

^a^Questionnaire is only completed by patients in the intervention group [the CET is completed on the platform]

## Definition of treatment adherence and dropout

In internet-based therapy, research it is often unclear how treatment adherence is defined and there seems to be no gold standard [42]. However, use of different definitions across studies makes comparisons difficult with respect to efficacy of internet-based therapy. In *eMindYourHeart*, we define treatment adherence by the number of modules that the patient completes. Since treatment needs of individual patients may vary and we have elective modules that will be allocated to patients based on their needs, a module is considered completed, when the therapist judges that the individual patient has worked sufficiently with the exercises in the module. For example, if a patient primarily suffers from depression and not anxiety, the module focusing on exposure therapy is likely not relevant. The therapist’s judgement is made according to guidelines specified in the treatment manual. This ensures consistency across therapists and enhances the fidelity of the study.

A patient is considered a dropout, if the patient actively informs the therapist that the patient wishes to stop treatment. A patient who, at some point during treatment, stops adhering to treatment and does not respond to the therapist, will not be considered a dropout, but will stay enrolled in the treatment until the end of the 12-week treatment duration.

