#### Secondary objectives

The secondary objectives are to evaluate the efficacy of the eHealth intervention targeting depression and anxiety + TAU as compared to TAU alone on symptoms of anxiety, perceived stress, health complaints, QoL, and dropout (number of patients dropped out in either arms at 3 months) at 3 months, and symptoms of depression, anxiety, perceived stress, health complaints, and QoL at 6 and 12 months’ follow-up and cost-effectiveness/cost-utility.

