#### Hypotheses

Given the user-centered, therapist-assisted eHealth approach to treat depression and anxiety, allowing patients to engage in the intervention when and where they want, we hypothesise that the intervention will be broadly acceptable to patients, have a low dropout rate and be effective and cost-effective.

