## Sample size calculation

Based on Stauber et al. [34], a conservative estimate of the standard deviation of the mean of the HADS depression score at 3 months is 3.5. The minimal clinically important difference for the HADS is 2 points [35]. For a normal-based comparison of independent means, with a power of 90% (ß = 0.1) and a risk of Type 1 error of 5% (α = 0.05), the estimated required number of patients is *n* = 66 in each group. Considering a potential 30% dropout rate, the estimated number of needed participants is *n* = 94 patients in each group (n (total) = 188).

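### Dropout is compared between arms at 3 months, but its only stated definition depends on telling a therapist, so it cannot be counted equally in both arms

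*Protocol article*

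**What the plan says.** The section on secondary objectives sets out to evaluate the intervention "as compared to TAU alone on symptoms of anxiety, perceived stress, health complaints, QoL, and dropout". The section on trial outcomes lists "trial dropout (number of patients dropped out in either arms at 3 months) and cost-effectiveness/cost-utility" among the secondary outcomes, and the abstract does the same. The hypotheses add that the intervention is expected to "have a low dropout rate and be effective and cost-effective".

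The only definition is in the section on treatment adherence and dropout: "A patient is considered a dropout, if the patient actively informs the therapist that the patient wishes to stop treatment". A patient who stops adhering and does not answer the therapist "will not be considered a dropout, but will stay enrolled in the treatment until the end of the 12-week treatment duration". The definition is not expressly limited to one arm.

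The sample size section uses the same word for a planning allowance: "Considering a potential 30% dropout rate", which takes 66 per group to 94. The ethics section says that any subject may leave the trial, and that those who drop out are still followed up under intention-to-treat. It gives no rule for counting them.

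**The concern.** A between-arm outcome needs an event that can occur, and be recorded, in the same way in both arms. The stated event is a message to a therapist about stopping treatment. Intervention patients have a therapist, modules, text messaging and scheduled calls. TAU patients receive standard cardiac rehabilitation, for which no trial therapist is described.

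Two separate results are at stake, and the rule pushes them in opposite directions:

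- **The comparison with TAU.** Only one arm has a regular channel through which the event is recorded, so the rule tends to make the intervention look worse.
- **The intervention arm's own rate.** Silent stoppers never count, so the rule tends to make the intervention look better. The hypothesis of a low dropout rate could be declared met while many patients had stopped using the programme.

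In both cases the figure reflects who has a therapist to notify, and who chooses to do so. It does not measure retention in the trial.

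**Working it through.** **1. Opportunity to be counted, by arm**

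| | TAU + eMindYourHeart | TAU alone | Section |
|---|---|---|---|
| Therapist interview before randomisation | yes | yes | Table 1 (recruitment) |
| Told allocation by therapist | yes | yes | Table 1 (recruitment) |
| Scheduled calls after allocation | 4 (weeks 1, 3, 6, 9) | none described | Contents; Treatment as usual |
| Text messaging with psychologist | yes | none described | Contents |
| Therapist-delivered treatment to stop | yes | none described | Contents; Treatment as usual |

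After allocation, the period that a 3-month count covers, the stated event has a regular route of ascertainment in one arm only.

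**2. Three uses of one word**

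- Definition section: an active statement to the therapist about stopping treatment. Silence is excluded.
- Trial outcomes: trial dropout, counted in both arms at 3 months, with no rule of its own.
- Sample size: the loss that inflates the required number. The statistical methods analyse patients who have a 3-month evaluation, so this must mean a missing 3-month score.

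The first and third are different events. A patient who notifies the therapist can still return the HADS, because dropouts are followed up. A patient who falls silent may return nothing and yet is not a dropout.

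**3. The plan's own sample size figure**

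Inputs from the sample size section: SD 3.5, difference 2, power 90%, α = 0.05 (two-sided assumed).

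- n per group = 2 × [3.5 × (1.960 + 1.282) / 2]² = 64.4, so 65. The t-test version gives 65.3, so 66, as stated.
- 66 / (1 − 0.30) = 94.3, stated as 94. Also 94 × 0.70 = 65.8.
- Power with 66 per group: 90.7%.

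The stated figures reproduce. They depend on the number of 3-month scores obtained, not on the dropout definition, so this point leaves them unchanged.

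**4. Illustration of the effect on the comparison (assumed rates)**

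Take the limiting case in which no TAU patient is counted, with 94 per arm. Fisher's exact test, two-sided:

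- 5 versus 0: p = 0.059
- 6 versus 0: p = 0.029

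Six counted dropouts in the intervention arm are therefore enough for nominal significance. Suppose the same true proportion q in each arm wishes to stop, and every such intervention patient says so. The chance of a spurious significant difference is P(X ≥ 6) with X ~ Binomial(94, q):

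| q (assumed) | P(X ≥ 6) |
|---|---|
| 5% | 33% |
| 10% | 92% |
| 15% | 99.7% |
| 20% to 30% | over 99.9% |

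The document gives no value for q. Its only related figure is the 30% planning allowance, which concerns a different event.

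**The case against.** The strongest reply is that two concepts are being run together. The outcome is called trial dropout, whereas the definition sits under a heading on treatment adherence, discusses modules and the 12-week treatment, and concerns stopping treatment. The ethics section has separate wording about leaving the trial, which TAU patients can do. On this reading the definition covers eHealth treatment only, and the rule for trial dropout is a detail left to the full protocol. This is a plausible account of what was intended. It does not settle the matter, because the article fixes a definition of a dropout without limiting it to one arm and gives no other. The gap is therefore a conflict between two stated items, not just an omitted detail.

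A second reply also has force. Silent stopping is not hidden altogether: adherence is measured by completed modules, and missing 3-month evaluations will show in the analysed numbers. That makes the information recoverable, but it does not repair the named outcome or the hypothesis attached to it.

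A reader might go further and infer that TAU patients cannot be dropouts at all, that their count is zero by construction, or that the 30% allowance predicts a particular split of counts between arms. The document does not support this. TAU patients speak to the therapist before and at allocation, later contact is not ruled out, and anyone may leave the trial. Those who notify are not a subset of those without data, and 30% is described only as a potential rate. A near-zero TAU count is a reasonable expectation under the literal rule; a structural zero is not established.

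**Conclusion.** The point holds as a problem of unequal ascertainment in a secondary outcome. As written, the dropout rule cannot be applied equally to the two arms, leaves out silent stoppers, and differs from the loss of 3-month data that the sample size allows for. Neither the comparison of dropout with TAU nor the low-dropout hypothesis can be interpreted under it.

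The size cannot be derived from the document. The 6-versus-0 threshold and the 33% and 92% figures assume no counted TAU dropouts, equal true rates in both arms, and full notification in the intervention arm. They show how little it takes to mislead; they are not forecasts. The conclusion also assumes that no separate counting rule exists elsewhere. If the full protocol has one, the task is to bring the article into line with it.

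The primary analysis and the sample size are not affected. The point should be fixed, but it does not threaten the trial's main conclusion.

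**What to change.** - Define trial dropout, as used in the secondary objectives and trial outcomes, by one rule observable in both arms: withdrawal from the trial or no 3-month HADS-D. State the cut-off for a late return, and show the two components separately.
- Count it over all randomised patients. The modified intention-to-treat set is limited to patients with a 3-month evaluation, so it cannot contain those who lack one.
- Report the between-arm difference in proportions with a confidence interval.
- Limit the existing therapist-notification rule to discontinuation of the eHealth treatment. Report it alongside silent non-use, as descriptors of the intervention arm only.
- Tie the low-dropout hypothesis to one of these named quantities, and use a different term for the 30% allowance, such as missing 3-month HADS-D.

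The cost is a change of wording. HADS-D is already scheduled at end of treatment and is not marked in Table 3 as restricted to one arm, so no new measure is needed. With 31 of 188 patients included at the reported date, the rule could be settled before any comparison of arms. The downside is that the intervention arm's dropout figure may look less favourable once silent patients without a 3-month score are counted.

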## Other measures

Information on patients’ demographic and clinical characteristics at baseline will be captured from patients’ medical records at the rehabilitation centre *or* the hospital, DHRD*, or* via purpose-designed questions. These questions will be included in the questionnaire sent to patients at baseline with standardised and validated measures (Table 3).

Measures of total health care costs measured in EUR will be collected from the Danish administrative health care registers. Loss of labour market productivity will be calculated using the human capital approach where average wages are used to estimate loss of work productivity. Costs will be measured in 2020 prices using a currency rate of 1 EURO to 7.45 DKK. Health care costs include all hospital utilisation aggregated using the Danish diagnosis-related group (DRG) prices (somatic and psychiatric care). Primary care services will be aggregated using national health insurance service fees (including GPs and private practicing specialists). Total utilisation of prescription drugs will be measured by purchasing prices of the patient excluding value added tax (VAT).

Cost-utility will be measured by estimation of the incremental costs for a gain in QoL. Costs will be covering intervention costs and 12-month total health care utilisation. Thus, the cost-utility analysis will be carried out using the perspective of the health care sector. QoL will be measured using HeartQoL at 3, 6 and 12 months. A probabilistic approach will be used to assess uncertainty and acceptability curves will estimated.

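### The cost-utility analysis is written on HeartQoL, while Table 3 assigns the EQ-5D-5L to that purpose and no analysis text uses it

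*Protocol article*

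**What the plan says.** The protocol article touches the point in three places.

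- **Other measures.** The health-economic paragraph defines the analysis: "Cost-utility will be measured by estimation of the incremental costs for a gain in QoL". It then names the instrument: "QoL will be measured using HeartQoL at 3, 6 and 12 months". On the cost side it says "Costs will be covering intervention costs and 12-month total health care utilisation", from the health care sector's perspective. On uncertainty it says "A probabilistic approach will be used to assess uncertainty and acceptability curves will estimated".
- **Patient-reported measures, Table 3.** HeartQoL (14 items) is entered under the construct of quality of life. The EQ-5D-5L (6 items) is entered under "Cost-effectiveness/cost-utility", with assessments at baseline, end of treatment, 6 and 12 months. The row does not carry the footnote that marks questionnaires given to the intervention group only.
- **Trial outcomes.** The secondary outcomes list "QoL (HeartQoL) at 3, 6, and 12 months follow-up" and, as a separate item, "cost-effectiveness/cost-utility".

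The EQ-5D-5L is named nowhere else in the article. The text contains no mention of QALYs, a utility index, a value set, or a mapping from HeartQoL to utilities.

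**The concern.** Two parts of the current text give the same analysis two different instruments. The table collects a generic utility instrument for cost-utility; the analysis paragraph puts a disease-specific score in its place.

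The choice decides what the result means. A cost-utility ratio needs an effect measured in preference-based utility, normally QALYs, so that it can be set against a willingness-to-pay value or against other uses of the same money. A cost per point on a heart-specific questionnaire does not permit that comparison. An acceptability curve built on it would have a horizontal axis in euros per HeartQoL point, for which the article offers no reference value.

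There is also the ordinary pre-specification problem. With two instruments attached to one analysis, the choice between them could be made after the results are known.

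**Working it through.** The plan states no figure for this analysis, so there is nothing to reproduce. The check sets the passages side by side and follows the written rule through.

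**Step 1. Which instrument feeds which analysis?**

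| Place in the article | HeartQoL | EQ-5D-5L |
|---|---|---|
| Other measures (cost-utility paragraph) | effect measure at 3, 6 and 12 months | not mentioned |
| Table 3 | quality of life | cost-effectiveness/cost-utility |
| Table 3, times | baseline, end of treatment, 6 and 12 months | baseline, end of treatment, 6 and 12 months |
| Trial outcomes | secondary quality-of-life outcome, listed apart from cost-utility | not mentioned |
| Statistical methods | longitudinal mixed model | not mentioned |

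The table and the outcome list keep HeartQoL and cost-utility apart. The cost-utility paragraph merges them.

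**Step 2. What does the written rule produce?** With ΔC the difference between arms in intervention plus 12-month health care costs, and ΔE the difference in effect:

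- Ratio = ΔC / ΔE. With E taken from HeartQoL, the unit is EUR per HeartQoL point.
- Acceptability curve = P(λ·ΔE − ΔC > 0), plotted over λ. With E taken from HeartQoL, λ is also in EUR per HeartQoL point.

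No step in the text converts the score to utilities, so neither output is in utility terms.

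**Step 3. Would the collected EQ-5D-5L data support the analysis?** Trial outcomes equates end of treatment with 3 months. Counting all visits from the same origin, the intervals are 0.25, 0.25 and 0.5 years. By the trapezium rule, with u the EQ-5D-5L index value at each month:

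QALY = 0.25·(u0 + u3)/2 + 0.25·(u3 + u6)/2 + 0.5·(u6 + u12)/2

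= 0.125·u0 + 0.25·u3 + 0.375·u6 + 0.25·u12

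The weights sum to 0.125 + 0.25 + 0.375 + 0.25 = 1 year. The scheduled assessments therefore cover a full 12 months, the same length as the cost horizon, in both arms. The defect lies in the specification and not in the data collection.

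**The case against.** The best defence has four parts.

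- *The article never promises a cost per QALY.* This is true. It defines cost-utility as cost per gain in quality of life. But it uses the term cost-utility, and its own table attaches a utility instrument to that term. The conflict does not depend on the word QALY.
- *Details of an economic analysis belong in a fuller plan.* An omission would be excused on that ground. Here the article positively names an instrument, and it is a different one from that in its table.
- *The EQ-5D-5L row in Table 3 carries a second marker whose footnote text is absent from the copy reviewed.* That footnote might show the intention. It would not alter what the cost-utility paragraph says.
- *That HeartQoL lacks utility weights is not stated in the article.* This is fair. It is general methodological knowledge. What the document itself shows is that it supplies no weights or mapping.

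Three stronger readings are tempting and should not be drawn.

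- Because the paragraph lists only 3, 6 and 12 months, a reader might infer that the gain is not adjusted for baseline. The text does not exclude adjustment: it speaks of a gain, Table 3 collects both instruments at baseline, and the months listed match the follow-up times in the outcome list.
- A reader might infer that the trial will produce no utility-based result. Table 3 shows an intention to use the EQ-5D-5L for this purpose, so the documents establish a conflict and not a certain loss.
- A reader might take the background's pairing of efficacy with cost-effectiveness to mean that half the aim is at risk. The primary objective is depression at 3 months; cost-effectiveness/cost-utility is listed among the secondary objectives.

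**Conclusion.** The point stands as a wrong specification of one secondary analysis. The cost-utility paragraph names HeartQoL, Table 3 assigns the EQ-5D-5L, and only one of them can be the effect measure. Taken literally, the paragraph gives a cost per HeartQoL point under the name of cost-utility, with acceptability curves that have no usable decision scale.

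The whole effect side of the cost-utility result is affected, and no numerical bias can be attached to it. The sample size, the primary analysis and the clinical secondary outcomes are untouched. The conclusion rests on the article's own text for the conflict, and on general knowledge that a heart-specific score is not a preference-based utility for its consequence. Because the outcome is secondary and the necessary data are already scheduled, this should be fixed but does not threaten the trial.

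**What to change.** In the cost-utility paragraph under Other measures:

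1. Replace HeartQoL with 12-month QALYs from EQ-5D-5L index values, calculated by area under the curve over baseline, 3, 6 and 12 months, with the comparison between arms adjusted for baseline utility. Name the value set.
2. State that the ratio and the acceptability curves are per QALY.
3. Keep HeartQoL as the secondary quality-of-life outcome. If a cost per HeartQoL point is also wanted, report it as a separately labelled cost-effectiveness ratio.

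The cost is a change of wording. The EQ-5D-5L is already scheduled at all four times in both arms, so no new data are needed. When the article reported its status, 31 of 188 patients had been included, so at that point the correction could have preceded most of the outcome data. It should in any case be made and dated before the economic data are analysed.
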